| 2. Study design The design will be a group-based comparison with phased introduction of the GeneXpert (*stepped-wedge* or *phased implementation* design).[[22]](#endnote-23) The units of comparison will be defined as smear examination laboratories together with the clinics that drain upon them for this laboratory service, as defined above. A group-wise comparison is preferred because the intervention will be introduced at the group level (i.e. in laboratories) and the impact of the intervention is thus best assessed at the group level as well. Also, designs with individual comparisons (e.g. individual randomization) will disrupt clinic and laboratory routine and therefore introduce artificial elements that may bias the outcomes (Hawthorne effect).  In this design, all units will start in the *baseline* group, i.e. diagnose TB following current procedures. Each unit will then at different points in time change to the *intervention* group i.e. do GeneXpert instead of smear examination, such that at the end of the observation period all units will be in the intervention group. The sequence by which the units move from baseline to intervention will be randomized. In that way all units will contribute to the person-time observation of both the baseline and the intervention group, but with different durations. This will allow before-after comparison while taking account of potential bias that would be introduced if e.g. case detection rates change over time for reasons not related to the intervention.  See figure 1 for graphic explanation of the design.  *Figure 1. Graphic representation of study design.* | | | | | | | | | |
| --- | --- | --- | --- | --- | --- | --- | --- | --- | --- |
| **Time** | month 1 | month 2 | month 3 | month 4 | month 5 | month 6 | month 7 | month 8 |  |
| **Unit** |  |  |  |  |  |  |  |  |  |
| 1 |  |  |  |  |  |  |  |  |  |
| 2 |  |  |  |  |  |  |  |  |  |
| 3 |  |  |  |  |  |  |  |  |  |
| 4 |  |  |  |  |  |  |  |  |  |
| 5 |  |  |  |  |  |  |  |  |  |
| 6 |  |  |  |  |  |  |  |  |  |
| 7 |  |  |  |  |  |  |  |  |  |
| 8 |  |  |  |  |  |  |  |  |  |
| 9 |  |  |  |  |  |  |  |  |  |
| 10 |  |  |  |  |  |  |  |  |  |
| 11 |  |  |  |  |  |  |  |  |  |
| 12 |  |  |  |  |  |  |  |  |  |
| 13 |  |  |  |  |  |  |  |  |  |
| 14 |  |  |  |  |  |  |  |  |  |
|  | | | | | | | | | |
|  |  | baseline | |  | intervention | |  |  |  |

*Randomization procedure*

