## 3. Intervention

The intervention will be the introduction of the GeneXpert assay as replacement of sputum smear microscopy in routine health care settings.

During the **baseline period** all patients suspected clinically of pulmonary TB will have sputum smear examination as per routine and current NTCP guidelines, i.e. two sputum samples will be sent with a request form to the microscopy facility. The result is then communicated back to the clinic. In case of one or two positive smear examinations the patient is diagnosed with smear-positive TB and treated accordingly. In case of two negative smears the diagnosis of smear-negative TB is made or rejected on clinical grounds, generally including chest X-ray examination and an assessment of the clinical response to broad-spectrum antibiotics. Repeat smear examination may be done, as may be mycobacterial culture in case the patient qualifies the NTCP selection criteria. Since culture results may take 4 to 8 weeks, the patient may be initiated on treatment before the result becomes available if the clinical condition so requires. A negative culture result then may or may not result in discontinuation of TB treatment.

During the **intervention period** all patients suspected clinically of pulmonary TB will have sputum examination as per routine and current NTCP guidelines, but instead of microscopic smear examination of two specimens, one sputum specimen will be submitted examined using the GeneXpert (Figure 2).The result is then communicated back to the clinic. In case of a positive result the patient is diagnosed with pulmonary TB and treated accordingly. In addition, microscopic sputum smear examination will be done to classify the patient as smear-positive or smear-negative for notification purposes. Note that this will *only be done in case of a positive GeneXpert result* (i.e. for the minority of TB suspects). In case of a positive Genexpert but a negative smear examination, a second sputum specimen will be requested before treatment initiation and examined microscopically in order to fulfill the notification criteria for smear-negative TB (i.e. TB with at least two negative smears).

In case of a negative GeneXpert result but continued clinical suspicion of TB the GeneXpert can be repeated after a time period determined by the clinical condition of the patient.

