## 4. Study endpoints

The study will have the following endpoints:

1. The change in incidence rates of diagnosed and notified bacteriologically confirmed pulmonary TB comparing the baseline to the intervention period, expressed per 100,000 population per annum. We will take the rate of diagnosed TB as well as that of notified TB since the latter is restricted to patients who are put on treatment within the public health system, and data show that 10-15% of the diagnosed cases are not notified. Bacteriological confirmation will be defined as: a positive microscopic smear examination *or* a positive culture with identification positive for *M. tuberculosis,* *or* a positive MTB signal in the GeneXpert assay.
2. The change in incidence rates of diagnosed, but not bacteriologically confirmed, pulmonary TB comparing the baseline to the intervention period, expressed per 100,000 population per annum.
3. The change in incidence rates of diagnosed and notified bacteriologically confirmed (by the GeneXpert) smear-negative pulmonary TB comparing the baseline to the intervention period, expressed per 100,000 population per annum. This is the measure in which the greatest impact is expected.
4. The change in proportion of diagnosed pulmonary TB patients who are ultimately diagnosed as having MDR-TB, comparing patients enrolled in the baseline period with patients enrolled in the intervention period.

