In our calculations C was fixed at 14, λ0 and λ1 were set as indicated below and the additional design effect was varied between 1.5 and 2.0, so that the parameter that changed as a result was y. Assuming fixed population sizes this thus resulted in a minimum observation period for each study arm in a classical group-randomized trial with concurrent allocation of the intervention and equal size, which was then multiplied by 2 to arrive at the total observation period for the stepped-wedge design. We repeated this for total observation periods of 24, 20, 16, 12 and 8 months.

The sample size was calculated based on an average rate of diagnosis of 50/100,000 per annum for the baseline period, and a baseline diagnosis rate of 10/100,000 per annum with bacteriological confirmation through culture (i.e. 20% of sputum smear-negative cases), with a total of 60/100,000 per annum. The minimum diagnosis rate that can then be observed as significantly different from this baseline rate would range from 93/100,000 for a duration of 24 months to 95/100,000 for a duration of 8 months assuming DEFFsw=1.5, and from 110/100,000 for a for duration of 24 months to 112/100,000 for a duration of 8 months assuming DEFFsw=2.0 (figure 2). Varying the average size of the populations served by each unit from 350,000 to 750,000 has very limited effect on these estimates. For a more conservative, “worst case” scenario of a baseline rate of 20/100,000 (i.e. 40% of all smear-negative TB is bacteriologically confirmed in the baseline period), the corresponding figures would range from 109 to 128/100,000, respectively.

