## 10. Data management and analysis

Over the end of the observation period, data from Manaus and Rio will be extracted from SINAN and GAL as described above. The routine procedures to check errors and linkage will be performed by the designated units in the Health Department, as per routine. This procedure includes checking for duplication, suspected incompatibilities, scale errors. Units are then informed. In Rio, [name] is responsible for this routine. In Manaus, by the municipal TCP manager, [name]. Once this procedure and linkage is done, the identification variables will be deleted and the following variables will be retained for analysis:

- From both SINAN and GAL: patient code, age, sex, health district of residence, sputum smear and culture resultsError: Reference source not found
- From SINAN only: clinic of notification, diagnostic classification (smear-positive/smear-negative/extrapulmonary), treatment history (new, previously treated), date of diagnosis, date of treatment initiation, HIV status, other major co-morbidities.
- From GAL only: positive sputum smear examination details (number of positive smears, highest smear grade obtained, date(s), laboratory); positive mycobacterial culture (number of positive cultures, identification, date(s), laboratory); drug susceptibility results (DST done yes/no, results for each drug tested, date(s), laboratory); positive GeneXpert (number of assays done; highest value obtained; rifampicin resistance yes/no/indeterminate, date(s), laboratory).

General data cleaning will be performed, including checks for duplicate entries, suspected mismatches, range errors, and results communicated to the responsible surveillance units for updating.

The patient code will be assigned for the analysis only and have no reference to patient identifiers.

The data analysis will be performed using STATA and will include:

- 1. Calculation of the number of diagnosed, bacteriologically confirmed pulmonary TB cases by smear status, for each unit, separately for baseline and intervention period.
  2. Calculation of the number of notified pulmonary TB cases, irrespective of bacteriological confirmation, by smear status and in various strata of age, sex and HIV status, for each unit, separately for baseline and intervention period.

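### As worded, endpoint 3 counts only smear-negative TB confirmed by GeneXpert, a test not used at baseline, which contradicts the protocol's own definition of confirmation, sizing and analysis list

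*Protocol*

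**What the plan says.** Protocol III.4 (Study endpoints) lists four endpoints and names none as primary. The third is the change in the rate of diagnosed and notified "bacteriologically confirmed (by the GeneXpert) smear-negative pulmonary TB comparing the baseline to the intervention period". The protocol adds that it expects its largest effect here.

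The sections that bear on this are:

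- **III.4, endpoint 1** defines bacteriological confirmation as a positive smear, or "a positive culture with identification positive for" *M. tuberculosis*, or a positive GeneXpert signal.
- **III.2 (Study design)** says that units which move to the intervention group "do GeneXpert instead of smear examination".
- **III.3 (Intervention)** says that at baseline "all patients suspected clinically of pulmonary TB will have sputum smear examination as per routine and current NTCP guidelines". Further work-up may include repeat smears, "as may be mycobacterial culture in case the patient qualifies the NTCP selection criteria".
- **III.5 (Sample size)** uses "a baseline diagnosis rate of 10/100,000 per annum with bacteriological confirmation through culture (i.e. 20% of sputum smear-negative cases").
- **III.10 (Data management and analysis), item 1** is "Calculation of the number of diagnosed, bacteriologically confirmed pulmonary TB cases by smear status, for each unit". Item 3 does the same for notified cases. Neither is limited to one confirming test.

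**The concern.** A before/after comparison needs a numerator that can be filled in both periods. The parenthesis in endpoint 3 ties confirmation to a test that a unit does not have until it crosses over. Smear-negative cases confirmed by culture at baseline are therefore left out of the comparator, and the baseline rate is zero by definition. The change so measured is simply the GeneXpert yield in the intervention period. It does not show whether GeneXpert confirms more smear-negative TB than smear plus selective culture.

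This matters because the protocol singles out this measure for the greatest expected impact, and because the study is meant to inform national adoption of the test. An analyst who followed the endpoint list literally would report a gain that the wording itself had created.

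**Working it through.** **Inputs (Protocol III.5).** 14 units; 500,000 inhabitants per unit; 8 months, on average 4 per unit in each period; k = 0.25; z values 1.96 and 0.84, multiplied by DEFFsw of 1.5 to 2.0; smear-negative confirmed baseline λ0 = 10/100,000 per annum.

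**1. Reproduce the plan's figures.** The formula is C = 1 + Z²[(λ0+λ1)/y + k²(λ0²+λ1²)]/(λ0−λ1)², with C = 14, Z = 2.8 × DEFFsw, and y = 500,000 × half the duration in years. Solving for λ1 with λ0 = 10 (per 100,000) gives:

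| DEFFsw | Duration | Computed λ1 | Stated |
|---|---|---|---|
| 1.5 | 24 months | 16.1 | 17 |
| 1.5 | 8 months | 17.6 | 18 |
| 2.0 | 24 months | 19.2 | 20 |
| 2.0 | 8 months | 21.4 | 22 |

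The stated figures are the computed ones rounded up. The text calls them increases, but they reproduce as intervention-period rates against a baseline of 10. With λ0 = 60 the same formula gives 92.8, 94.5, 109.2 and 111.7, matching the stated 93, 95, 110 and 112. The sizing for smear-negative TB therefore rests on a non-zero, culture-based baseline.

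**2. Baseline cases lost under the literal wording.** Person-time per period is 14 × 500,000 × 4/12 = 2.33 million person-years. At 10/100,000 that is about 233 expected cases, all counted as 0. At 20/100,000, the protocol's worst-case figure, it would be about 467.

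**3. No true gain.** Suppose GeneXpert confirms only the 10/100,000 that culture already confirmed. With any-method confirmation the comparison is 10 versus 10, ratio 1. With the literal wording it is 0 versus about 233 cases. Using the variance in the formula, with y = 1.667 (in 100,000 person-years) and C − 1 = 13:

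- variance = (10/1.667 + 0.0625 × 100)/13 = (6 + 6.25)/13 = 0.942
- z = 10/√0.942 = 10.3, or 6.9 and 5.2 after division by DEFFsw 1.5 and 2.0

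At 72.5% of that yield (the single-sample sensitivity in smear-negative specimens quoted in the Introduction), the rate is 7.25/100,000 and z is still 4.7 at DEFFsw 2.0.

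**4. Detectable rate with a zero baseline.** With λ0 = 0 the formula reduces to C = 1 + Z²[1/(yλ1) + k²], so λ1 = 1/{y[13/Z² − k²]}. At 8 months:

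- DEFFsw 1.5: Z² = 17.64; λ1 = 1/[1.667 × (0.737 − 0.0625)] = 0.9/100,000
- DEFFsw 2.0: Z² = 31.36; λ1 = 1/[1.667 × (0.4145 − 0.0625)] = 1.7/100,000

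These compare like for like with 17.6 and 21.4 in step 1: same formula, power, k and DEFFsw.

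**The case against.** The strongest reply is that the parenthesis is a slip. The definition under endpoint 1, the sizing and the analysis list all point to confirmation by any method, and the wording of endpoint 3 is the only outlier. That is probably right about intent, but nothing in the protocol corrects the wording, and the endpoint list is the natural place to look for the definition.

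Three stronger readings are tempting, and the protocol does not support them.

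- **The planned analysis fails.** A reader might infer that the rate ratio in item 4 is undefined and that the Poisson model in item 5 has no finite estimate. Those items work on the counts in items 1 to 3, which are not limited to GeneXpert. Culture-confirmed baseline cases are in them, so the denominators are not empty.
- **A handful of cases would suffice.** Six cases against none gives a two-sided p of 2 × 0.5⁶ = 0.031, which is 0.26/100,000. This is a bare significance threshold that ignores variation between units and DEFFsw, so it cannot be set against 18–22/100,000, which are rates detectable with 80% power. The comparable figure is 0.9–1.7.
- **The result is bound to be positive and the power claim falls.** The first holds only if the literal wording is what gets analysed. The power claim is computed from the baseline of 10 and stands apart from the parenthesis.

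One further point stands. In the intervention period, III.3 has smear done only after a positive GeneXpert. Smear-negative status is then assigned almost entirely among GeneXpert-positive patients, which may be why the parenthesis is there. Deleting it does not by itself make the two periods symmetric.

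**Conclusion.** Endpoint 3 is wrong as written: its baseline is zero by definition, and it conflicts with three other parts of the protocol. Under the literal reading about 233 expected baseline cases vanish, and a yield equal to culture would look like a large effect (z of about 5 even at DEFFsw 2.0). The detectable rate would be more than ten times lower than the one the study was sized for.

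These sizes rest on the protocol's planning assumptions: equal populations of 500,000, equal person-time in the two periods, k = 0.25 and a culture-confirmed baseline of 10/100,000. The existence of the contradiction depends on none of them. It is confined to endpoint 3. Endpoints 1 and 2, the randomization, the data collection and the listed analyses do not depend on the parenthesis.

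**What to change.** 1. Remove the parenthesis that names GeneXpert, and define endpoint 3 as smear-negative pulmonary TB confirmed by culture or GeneXpert, in both periods. This matches endpoint 1, the sizing baseline and items 1 and 3.
2. State how a culture-positive, GeneXpert-negative case without a smear in the intervention period is classified. One way is to report the endpoint with such cases counted and not counted. Items 1 and 3 need the same rule, since they also split by smear status.
3. Report the number confirmed by GeneXpert alone as a description of the intervention period, without a before/after test.

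The cost is a small wording change, one extra sensitivity analysis and a smaller reported effect. The culture and GeneXpert results needed are already among the variables to be extracted from the laboratory system.

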In Brazil, smear examinations are widely available for patients with TB suspicion, free of charg for patients, in public health units. Culture is only recommended by the National TB Control Program (NTCP) in patients with previous history of TB, in PLHA, when treatment failure is suspected by the end of the second month of treatment, in difficult to obtain specimens, in extrapulmonary TB and in contacts of a resistant TB index case. Since sputum smear examination has a low sensitivity, the bulk of smear-negative TB diagnoses is made clinically without microbiological confirmation.[[5]](#endnote-6) In addition, despite the official recommendations, according to data from the NTCP, only 72% of new cases and only 17% of retreatment cases perform culture.Error: Reference source not found If added to cases with a negative sputum smear, at present, only one third of Brazil’s notified new cases are bacteriologically confirmed. It is estimated that 20% of these cases are not true TB cases (false positive diagnosis), resulting in delayed diagnosis of the true disease and unnecessary exposure to hepatotoxic antituberculous drugs. In conclusion, the limitations of the currently available tests for TB result in delayed diagnosis and unnecessary treatment.[[6]](#endnote-7),[[7]](#endnote-8)

In order to increase the detection of sensitive TB and to accelerate the diagnosis of resistant TB, the NTCP had the plan, in 2010, to implement universal culture (for every patient suspect of TB). Nevertheless, at present, the national laboratories that perform culture and DST, the state LACENs (Laboratório Central Noel Nutels) cannot absorb this workload, a great investment would be necessary.

A novel test platform has been developed, which is based on rapid real-time PCR. The all-in-one cartridge method allows use outside specialized laboratories. A version for detection of *M. tuberculosis*, the GeneXpert, has been developed with funding by FIND, the Foundation for Innovative New Diagnostics. Controlled trial in over 1700 TB suspects showed a sensitivity of 92.2%, representing a significant gain vis-à-vis sputum smears. In sputum smear negative samples, the sensitivity of GeneXpert® is 72.5% in one sample and reaches 90.2% in three samples.[[8]](#endnote-9)-[[9]](#endnote-10)[[10]](#endnote-11)[[11]](#endnote-12)[[12]](#endnote-13)[[13]](#endnote-14)[[14]](#endnote-15)[[15]](#endnote-16)[[16]](#endnote-17)[[17]](#endnote-18)[[18]](#endnote-19)[[19]](#endnote-20)

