As it will be afore detailed, the present rollout study proposes a change in the laboratory routine, not in the primary care health units (PCU). Randomization and data analysis will not be individual, but by laboratory/PCU. There is consistent evidence that this change will bring benefits to patients and their contacts, since an early bacteriologically confirmed diagnosis is foreseen, with consequent reduction in transmission. It is expected that this study will provide the NTCP with information for decision making regarding implementation of the technology, necessary personnel training, impact of the test in PCU and laboratory routines and other operational information.

In addition to the increased detection rate, secondary benefits from the substitution of GeneXpert for smears are expected, such as reduction of diagnosis delay of sensitive and drug-resistant TB, of morbidity, mortality and transmission. The reduction in the time to diagnosis of MDR-TB will allow the early treatment with second-line drugs recommended in these cases, also reducing morbidity and mortality, offering less opportunity for MDR-TB transmission. Finally, a reduction in the number of cases erroneously treated as TB is expected. Thus, this project ultimately intends to contribute to TB control in the country.

We emphasize that the present protocol includes only the operational pilot implementation study, other protocol submissions will follow for cost-effectiveness and acceptability studies. The validation study, previously submitted, was approved by CONEP and should be started in March 2011.

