## 2. Objectives

To estimate, in the routine of public health facilities of two municipalities in Brazil, the impact of the implementation of the GeneXpert assay on

- the case detection of pulmonary TB, measured by the change in rate of notification and treatment registration of bacteriologically confirmed TB, after introduction of the GeneXpert assay as a replacement of sputum smear microscopy in the routine health care settings.
- the detection of MDR-TB

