  3. Calculation of the number of notified, bacteriologically confirmed pulmonary TB cases by smear status and in various strata of age, sex and HIV status, for each unit, separately for baseline and intervention period.
  4. Calculation of rates for each of these three, by dividing the numbers summed over all units and strata by the summed population denominators, separately for baseline and intervention period, with their 95% confidence intervals, and calculation of the rate ratios and rate differences comparing the two periods with appropriate significance testing.
  5. Multivariate analysis of the observed rate ratios using Poisson regression to adjust for potential confounding due to unbalanced randomization by age, sex, history of TB treatment, HIV status (as far as available), unit and month of enrollment.
  6. Similar calculation of numbers, rates, rate ratios and rate differences by HIV status (as far as available).
  7. Calculation of proportion of diagnosed pulmonary TB patients who are ultimately diagnosed as having MDR-TB, by smear status at initial diagnosis, for each unit, separately for baseline and intervention period.
  8. Calculation of the risk ratios and risk differences for these proportions comparing the two periods with appropriate significance testing.
  9. Multivariate analysis of the observed risk ratios using logistic or log-linear regression (as appropriate, depending on observed proportions) to adjust for potential confounding due to unbalanced randomization by age, sex, history of TB treatment, HIV status (as far as available), unit and month of enrollment.
  10. Calculation, for patients ultimately identified with MDR-TB, of the time interval between diagnosis of pulmonary TB and detection of rifampicin resistance, by smear status at initial diagnosis, for each unit, separately for baseline and intervention period.
  11. Calculation, for patients ultimately identified with MDR-TB, of the time interval between diagnosis of pulmonary TB and initiation of second-line treatment, by smear status at initial diagnosis, for each unit, separately for baseline and intervention period.
  12. Calculation of differences for these time intervals comparing the two periods with appropriate significance testing.

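### Endpoint 4, the only MDR-TB endpoint, divides by an undefined group of diagnosed patients that GeneXpert is expected to change; a population rate should be reported beside it

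*Protocol*

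**What the plan says.** Protocol, II.2 Objectives, lists two targets. The second is "the detection of MDR-TB", with no measure attached.

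Protocol, III.4 Study endpoints, lists four endpoints. The first three are changes in rates per 100,000 population per annum. The fourth is "The change in proportion of diagnosed pulmonary TB patients who are ultimately diagnosed as having MDR-TB".

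Protocol, III.10 Data management and analysis, keeps that denominator. Item 7 is "Calculation of proportion of diagnosed pulmonary TB patients who are ultimately diagnosed as having MDR-TB, by smear status at initial diagnosis", and items 8 and 9 add risk ratios, risk differences and adjusted regression. Population rates come from item 4, "Calculation of rates for each of these three, by dividing the numbers summed over all units and strata by the summed population denominators". The three counts meant there are TB case counts, not MDR-TB counts. Items 10 to 13 add times to resistance detection and to second-line treatment.

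Protocol, I. Introduction, expects the number of diagnosed patients to move both ways: "In addition to the increased detection rate, secondary benefits from the substitution of GeneXpert for smears are expected", and "a reduction in the number of cases erroneously treated as TB is expected".

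**The concern.** A population denominator cannot be altered by the test. The number of diagnosed TB patients can be, and changing it is a purpose of the intervention. Endpoint 4 therefore combines the effect on MDR-TB found with the effect on TB found, which endpoints 1 to 3 already measure. The proportion could stay flat or fall while more MDR-TB is found, or rise with no additional MDR-TB case.

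The denominator is also unclear. Endpoint 2 and the sample-size assumptions (III.5) use the word diagnosed so as to include unconfirmed cases. Yet the only count of diagnosed cases planned in III.10 (item 1) is restricted to bacteriologically confirmed ones; items 2 and 3 count notified cases. The two readings give distortions of different size and sign.

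At stake is how one of the two objectives is reported to the national programme.

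**Working it through.** **Inputs (Protocol, III.5 Sample size).** 14 units ("In our calculations C was fixed at 14"); 500,000 inhabitants per unit; all diagnosed pulmonary TB 100 per 100,000 per year; confirmed TB at baseline 50 + 10 = 60; z values 1.96 and 0.84, multiplied by DEFFsw of 1.5 or 2.0; k = 0.25; 8 months in total, on average 4 per period.

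**1. Reproduce the protocol's detectable rates.** The stated formula is C = 1 + z²[(λ0+λ1)/y + k²(λ0²+λ1²)]/(λ0−λ1)². Set C = 14 and λ0 = 60, with rates per 100,000 and y in units of 100,000 person-years. For 8 months, y = 5 × 4/12 = 1.667.
- DEFFsw 1.5: z = 2.8 × 1.5 = 4.2. Solving gives λ1 = 94.5 (stated 95); for 24 months 92.8 (stated 93).
- DEFFsw 2.0: z = 2.8 × 2.0 = 5.6. Solving gives λ1 = 111.7 (stated 112); for 24 months 109.2 (stated 110).

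The stated figures reproduce. They are minimum detectable rates, not forecasts, and 110 to 112 exceeds the 100 assumed for all diagnosed TB, so it is an outer bound.

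**2. Identity.** Endpoint 4 risk ratio = (MDR-TB rate ratio) / (diagnosed-TB rate ratio). The baseline MDR-TB proportion cancels.

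**3. Denominator read as confirmed TB.**
- Break-even rise in MDR-TB found: 93/60 = 1.55; 95/60 = 1.58; 112/60 = 1.87. MDR-TB found must rise by 55% to 87% before the proportion rises at all.
- MDR-TB found unchanged: 60/93 = 0.65 to 60/112 = 0.54.
- MDR-TB found up 50%: 1.5/1.583 = 0.95 at 95; 1.5/1.867 = 0.80 at 112.
- Milder illustration: suppose every smear-positive case is still detected, all false diagnoses disappear (the Introduction's 20%, applied here to the 40 unconfirmed cases), and GeneXpert finds 72.5% of the remaining 42 smear-negative cases. The confirmed rate is then 50 + 0.725 × 42 = 80.45. Break-even is 80.45/60 = 1.34, and a 50% rise in MDR-TB found shows as 1.5/1.34 = 1.12.

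**4. The same in counts.** Person-years per period: 14 × 500,000 × 4/12 = 2.33 million. Confirmed cases: 1,400 at a rate of 60, and 2,217 at 95. Assume 2% MDR-TB at baseline (not in the documents): 28 cases, rising by 50% to 42. The population rate goes from 1.2 to 1.8 per 100,000 per year, a ratio of 1.50. The proportion goes from 28/1,400 = 2.00% to 42/2,217 = 1.89%, a ratio of 0.95. At 1% or 5% the baseline count is 14 or 70 and the ratios are the same.

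**5. Denominator read as all diagnosed TB.** The documents give no intervention-period total, so 80 to 120 is an assumed range around 100. With MDR-TB found unchanged:
- total falls to 80: 100/80 = 1.25
- total falls to 92 (all of 0.2 × 40 = 8 false diagnoses removed, nothing added): 100/92 = 1.09
- total stays at 100: 1.00, so the proportion ratio equals the rate ratio
- total rises to 120: 100/120 = 0.83

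**6. Smear strata.** At baseline, suspects have two smears. In the intervention period smear is done only after a positive GeneXpert (III.3). Smear-positive patients should be diagnosed in both periods, so that stratum is largely comparable. The smear-negative stratum is not: at baseline it rests mostly on clinical diagnosis, and under the intervention on GeneXpert-positive patients. Adjusting for age, sex, treatment history, HIV, unit and month does not undo a change in who enters the group.

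**The case against.** The objective names no measure, and the share of diagnosed patients found to have MDR-TB is a coherent measure of resistance ascertainment. The MDR-TB rate is the TB rate times this share. A flat share with more TB correctly says that ascertainment per patient did not change, while endpoint 1 reports the extra TB. This stands. A reader might infer that endpoint 4 cannot answer the objective at all; the documents do not support that. It answers a narrower question.

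A reader might also infer that a flat or falling result is the likely one. That is not supported either. Baseline culture, the route to susceptibility testing, is selective: "only 72% of new cases and only 17% of retreatment cases perform culture". GeneXpert tests for rifampicin resistance as part of the assay, so the numerator may outgrow the denominator.

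The larger distortions require the confirmed-only reading, and the protocol's wording elsewhere leans towards all diagnosed TB. This stands as well, but the text does not settle it.

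The smear-positive stratum in item 7 already gives a nearly unaffected comparison, and items 10 to 13 add timing measures. Both help in part. The first leaves out the smear-negative patients, in whom endpoint 3 expects the greatest impact. The second covers only patients already found to have MDR-TB.

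Finally, a proportion avoids the population denominator, which III.11 calls difficult to assign for the main Manaus policlinic (PCF). This is true, but endpoints 1 to 3 already carry that problem.

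**Conclusion.** The point holds in a limited form. As the sole MDR-TB endpoint, the proportion can misstate the change in MDR-TB detection in either direction, because its denominator is affected by the intervention and is not defined.

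On the confirmed-TB reading, a 50% gain in MDR-TB found would appear as 0.95 if the confirmed rate reached 95 per 100,000, and as 1.12 in the milder illustration at 80.45. On the all-diagnosed reading, the distortion over an assumed 80 to 120 per 100,000 runs from 1.25 to 0.83, and is nil at 100. The ratios do not depend on the baseline MDR-TB proportion. They do depend on the intervention-period TB rate, for which the protocol gives no forecast.

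The proportion is not invalid and need not be demoted. What is missing is a population-based MDR-TB measure beside it.

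**What to change.** 1. State in endpoint 4 and in items 7 to 9 whether the denominator is bacteriologically confirmed or all diagnosed pulmonary TB.
2. Add, as a co-reported MDR-TB endpoint, the change in the rate of diagnosed MDR-TB per 100,000 population per annum. Analyse it with the same rate calculation and Poisson model as endpoints 1 to 3 (items 4 and 5), keeping each patient in the period of enrolment as endpoint 4 does now.
3. Keep the proportion as the measure of MDR-TB yield per diagnosed patient. Show it with the share of patients who have a rifampicin result, which the GAL variables in III.10 supply.
4. Treat the smear-positive stratum as the more comparable one, and caution against comparing the smear-negative stratum between periods.

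The cost is wording and one further analysis; no new data are needed. There are two downsides. MDR-TB counts are small: with 28 and 42 cases, the standard error of the log rate ratio, ignoring clustering, is √(1/28 + 1/42) = 0.244, so a ratio of 1.50 has a 95% interval of about 0.93 to 2.42. The proportion is nearly as imprecise, because the same counts dominate its variance. The uncertain PCF catchment also enters the rate, as it already does for endpoints 1 to 3.
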